### **Sample size determination**

Our single-center study results indicated that the probability of stroke deterioration was approximately 10.8% in the aspirin group and 6.1% in the DAPT group. Considering the 10.8% recurrent stroke rate in the aspirin group and the 6.1% recurrent stroke rate in DAPT group, a p value < 0.05 indicating statistical significance at the 95% confidence interval, and a 10% drop out rate, the target number of participants will be at least 2500; PASS 22.0 will be used to perform sample size calculation.

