### **Follow-up time**

The follow-up time for the two groups will be 90 days and 1 year. Vascular events were prospectively observed during hospitalization and during a 3-month follow-up period after the qualifying event via routine clinic visits or telephone interviews performed by experienced physicians with a predefined protocol. To ensure the accuracy of the outcome captured and to minimize inter-interviewer discrepancy, a set of uniform structured questionnaires was used by trained personnel. Enrollment will stop on November 31, 2021.

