### **Outcomes**

We set a composite vascular event (ischemic stroke, TIA, symptomatic intracerebral hemorrhage, myocardial infarction or angina attacks, and vascular death) as the primary outcome at 90 days. Recurrent ischemic stroke: (1) sudden onset of a new focal neurologic deficit, with clinical or imaging evidence of infarction lasting  $\geq 24$  hours and not attributable to a nonischemic cause (i.e., not associated with brain infection, trauma, tumor, seizure, severe metabolic disease, or degenerative neurologic disease), and (2) a new focal neurologic deficit lasting  $< 24$  hours and not attributable to a nonischemic cause but accompanied by neuroimaging evidence of new brain infarction. Imaging indicated that the new infarct should be geographically distinct from the original infarct. Progressive ischemic stroke: rapid worsening of an existing focal neurologic deficit (NIHSS increasing  $\geq 4$ , excluding hemorrhagic transformation after infarction or symptomatic intracranial hemorrhage) lasting  $> 24$  hours and not attributable to a nonischemic cause, accompanied by new ischemic changes from the initial infarct on baseline magnetic resonance imaging or computed

tomography of the brain. Symptomatic intracerebral hemorrhage was defined as acute infiltration of blood into the brain parenchyma or subarachnoid space with associated neurological symptoms and imaging findings with an increase in the NIHSS score of four or more points. Any subject who had rapid resolution of symptoms and no brain imaging suggesting tissue infarction was considered to have had a TIA. Any patient initially diagnosed with stroke who did not have further brain imaging with evidence of infarction but had complete resolution of symptoms within 24 hours were considered to have had a TIA. Myocardial infarction was confirmed if one had more than two from below: typical chest pain, Troponin elevation, ECG changes (new ST segment changes, new Q wave, or new left bundle branch block). vascular death if definition as death due to vascular events. Further efficacy exploratory analysis of mRS score changes (continuous) was performed and dichotomized at percentages of 0 to 2 versus 3 to 6 at the 3-month and one-year follow-ups.

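### The MI definition asks for more than two of three criteria, literally all three, so a non-fatal infarction without typical chest pain has no route into the primary composite

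*Protocol*

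**What the plan says.** The Outcomes section of the protocol fixes the rule for MI: "Myocardial infarction was confirmed if one had more than two from below: typical chest pain, Troponin elevation, ECG changes". The third criterion is spelled out in a bracket: "ECG changes (new ST segment changes, new Q wave, or new left bundle branch block". These ECG findings are alternatives joined by *or*, so they read as one criterion and the list has three items.

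MI belongs to the primary outcome, whose later components are "symptomatic intracerebral hemorrhage, myocardial infarction or angina attacks, and vascular death) as the primary outcome at 90 days". Angina attacks have no definition. Vascular death has one that does not depend on the MI criteria: "vascular death if definition as death due to vascular events".

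Under Follow-up time, vascular events are observed in hospital and then for three months "via routine clinic visits or telephone interviews performed by experienced physicians with a predefined protocol". Nothing elsewhere in the protocol relaxes the MI threshold or restates it as two or more.

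**The concern.** More than two of three leaves only three of three. An event with raised troponin and a new Q wave but no typical pain is then not an MI. Nor is an event with pain and raised troponin but an unremarkable ECG.

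The threshold governs a named component of the declared primary outcome, and the protocol itself sets it, so it is not a detail left for a later document. Two things are at stake:

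- Some genuine non-fatal infarctions may be left out of the composite.
- Others may be recorded under an undefined angina category, where whether they count depends on judgement.

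Centres that read the phrase differently, some as all three and some as at least two, would also classify the same event differently.

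**Working it through.** The protocol gives no figure for this point, so there is none to reproduce. The check has two parts.

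**1. Which patterns qualify.** Three criteria, each present or absent, give 2³ = 8 patterns.

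- More than two of three: 1 of 8 patterns confirms MI (pain + troponin + ECG).
- At least two of three: 4 of 8 patterns confirm MI.

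The three patterns on which the rules differ, followed into the composite as written:

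| Pattern | MI as written? | Other route into the composite if non-fatal |
|---|---|---|
| Troponin + ECG, no pain | No | None evident |
| Pain + troponin, no ECG change | No | Angina attack (undefined) |
| Pain + ECG, no troponin | No | Angina attack (undefined) |

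A fatal case of any pattern can enter as vascular death. The clear loss from the composite is therefore the first row, non-fatal only.

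**2. Illustrative size.** The protocol does not say how often each criterion is met in true infarctions, so the inputs are assumptions: pain p = 0.80 (range 0.60 to 0.90), troponin t = 0.95, ECG e = 0.80 (range 0.70 to 0.90), independent of each other. Let every painful infarction enter as MI or angina, and set fatal cases aside.

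- Composite capture as written = p
- Composite capture under at least two = p + (1 − p) × t × e
- Gap = (1 − p) × t × e

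| p, t, e | As written | At least two | Gap |
|---|---|---|---|
| 0.80, 0.95, 0.80 | 80% | 0.80 + 0.20 × 0.95 × 0.80 = 95.2% | 15.2 points |
| 0.60, 0.95, 0.70 | 60% | 0.60 + 0.40 × 0.95 × 0.70 = 86.6% | 26.6 points |
| 0.90, 0.95, 0.90 | 90% | 0.90 + 0.10 × 0.95 × 0.90 = 98.6% | 8.6 points |

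The rows pair low with low and high with high. Mixed corners of the same ranges widen the gap: 0.10 × 0.95 × 0.70 = 6.7 points at the least and 0.40 × 0.95 × 0.90 = 34.2 points at the most.

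Capture under the MI label alone is a different quantity. In the central case all three criteria are met in 0.80 × 0.95 × 0.80 = 60.8%, and at least two in 0.608 + 0.152 + 0.032 + 0.152 = 94.4%. That difference includes painful events that can still reach the composite as angina.

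The step from capture of infarctions to the composite event rate cannot be taken. No MI or angina rate is stated, and the sample size rests on stroke alone: "Considering the 10.8% recurrent stroke rate in the aspirin group and the 6.1% recurrent stroke rate in DAPT group".

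**The case against.** **It is probably a slip of language.** The English is loose elsewhere: the vascular death sentence is ungrammatical, and Follow-up time gives a 31 November. At least two may well have been meant. That is plausible, but the protocol does not settle it. The same section states an inclusive threshold plainly for symptomatic haemorrhage (an NIHSS increase of four or more), so a reader has no textual reason to take this one as inclusive. A slip in an outcome rule still needs correcting.

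**The ECG findings could be counted separately.** With five items, more than two means at least three. Troponin with both a new ST change and a new Q wave would then qualify without pain. Pain plus troponin alone would still fail, as would troponin plus a single ECG finding. The bracket and the *or* do not favour this reading, and it rescues only part of the loss.

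**Most affected events stay in the composite.** This stands. A reader might infer that every infarction lacking pain or lacking ECG change drops out of the primary outcome, and take 61% versus 94% as the size of the loss. The documents do not support that, because angina attacks and vascular death are also components. For painful events the harm is a wrong label under an undefined heading.

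**No effect on the treatment comparison is shown.** This also stands. A reader might infer that the rule favours one group, since treatment is not randomized and the only blinded reading described is of neuroimaging. But one threshold applies to both groups, and nothing in the protocol gives a direction of bias. The stated hypothesis, the sample size and the survival and Cox analyses all concern stroke.

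**Conclusion.** The defect is real but minor. As written, the rule needs all three criteria. A non-fatal infarction with raised troponin and new ECG change but no typical chest pain therefore has no route into the 90-day primary composite. Infarctions with pain and only one other criterion lose the MI label and can enter only as undefined angina.

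Under the assumed frequencies, the composite captures about 80% of non-fatal infarctions as written and about 95% under at least two; the paired end cases are 60% versus 87% and 90% versus 99%. These figures rest on assumed inputs, on independence of the criteria, and on every painful event being recorded as MI or angina.

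The effect on the primary result is unknown, for want of an MI or angina rate. It is probably small, because the stated hypothesis and sample size are built on stroke. The protocol does not show which threshold was actually applied.

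**What to change.** Replace more than two with *at least two of the three*. Apply the rule uniformly to all suspected cardiac events from existing records, blind to treatment group. If the all-three rule was in fact used, disclose it and report which events change class.

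The cost is one phrase and a brief re-check of what should be a few events. Specificity falls slightly: chest pain with ECG change but no troponin elevation would now be confirmed as MI. Such an event could already enter the composite as angina, so in that pattern mainly the label changes. The composite itself gains the pattern of troponin plus ECG change without pain.

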## **Statistical analysis**

Continuous variables that are normally distributed will be presented as the mean value and SD. When variables were not normally distributed, they were presented as medians and IQRs. Count data will be described with n (%). Student's t test was used for continuous variables, and the Pearson  $\chi^2$  test was used for categorical variables. To compare the survival curve and survival rate of stroke recurrence, survival analysis will be conducted. Cox proportional hazard models will be used to explore the risk

factors for recurrent ischemic stroke. Propensity score matching will be used to control for confounding factors. All analyses were performed in SPSS 26.0 and the statistical software package R (<http://www.R-project.org>, The R Foundation).

## Discussion

An important treatment strategy for patients with acute ischemic stroke is to prevent deterioration and recurrence of stroke. The treatment standard for patients with acute minor ischemic stroke has not been well established. The CHANCE and POINT trials have shown that DAPT is superior to aspirin alone in patients with minor ischemic stroke (NIHSS score  $\leq 3$ ) or high-risk TIA. A South Korean registration study showed that more than 70% of patients with a NIHSS score 4-7 treated with DAPT within 24 hours of onset were also affected. Therefore, the optimal time frame to start DAPT post stroke to achieve efficacy remains unclear. Patients with AIS can present within 24 hours, 48 hours, 72 hours, and even 7 days post onset. DAPT may be the only method for preventing early deterioration in late presenters. A meta-analysis of dual versus mono antiplatelet therapy for acute non-cardioembolic IS or TIA patients within 3 days of symptom onset showed that compared with aspirin alone, DAPT was associated with a significant reduction in stroke recurrence (RR, 0.70; 95% CI, 0.59–0.82;  $P < 0.001$ ). The latest meta-analysis showed that DAPT can benefit patients if given within 3 days of onset.

In this proposed trial, loss to follow-up may occur. To prevent such a potential problem, the researchers will implement several methods for securing the follow-up. In addition, because of its multicenter design, confounding bias and selection bias will be well controlled. This trial to explore the efficacy and safety of dual antiplatelet therapy in patients with acute minor stroke (NIHSS score  $\leq 5$  and onset within 72 hours). Regardless of positive or negative results, the trial will provide valuable evidence on the appropriate treatment for this stroke population.

